### Recruitment and Informed Consent

HCPs assigned as data collectors will identify potential study participants who meet the inclusion criteria from hospital wards, community health care units, rehabilitation centers, or physiotherapy clinics and inform them verbally about the study. The HCPs will also inform them that participation is voluntary and that they have the right to withdraw from the study at any time. In addition, the HCPs will provide participants with written information and an informed consent form in English or, when appropriate, in Luganda. Each participant will sign a consent form for voluntary participation, which emphasizes their right to withdraw from the study at any time, in accordance with the Helsinki Declaration [50]. Before patients are included, a randomization sequence will be created by the second and last authors using a random number table developed by a researcher at Karolinska Institutet in Solna, Stockholm County, Sweden. After completion of the baseline assessment, the researcher in Uganda (JK) will contact the researchers at Karolinska Institutet to obtain information on group allocation. If a participant is allocated to the IG, the researcher in Uganda (JK) will contact the HCP and inform them to provide the intervention.

The participants who consent to take part in the study will be asked to identify a family member to enroll in the study. Potential participating family members will receive verbal and written information, and written informed consent will be obtained from those who agree to participate.

### Data Collection

After informed consent is obtained, demographic data collection and baseline assessments will be performed by data collectors (HCPs at the 3 participating centers). The data collectors are not involved in delivering the intervention and are blinded to the allocation of the intervention. All data collectors will receive training before data collection to standardize data collection procedures. All information will be collected face-to-face. Demographic data (Multimedia Appendix 3) and baseline assessments will be conducted after enrollment, and follow-up assessments will be conducted within 1 week after the intervention ends and at 6 months after inclusion, preferably by the same assessors.

### Primary Outcomes

#### Persons With Stroke

The COPM assesses an individual’s perceptions of performance and satisfaction in valued daily activities within the areas of self-care, productivity, and leisure [38]. For the initial evaluation, the COPM starts with a semistructured interview lasting 30 to 40 minutes during which the persons with stroke identify activities in everyday life that they consider to be important but difficult to perform. Each activity is documented, and the participants rate the importance of each activity on a 10-point scale. They are then asked to choose 3 relevant activities and rate their performance and satisfaction with performance in each activity on separate scales, where a higher score indicates greater importance, better performance, and greater satisfaction. For the re-evaluation at the end of the intervention period, the participants are again asked to rate their performance and satisfaction in each activity. A difference of ≥2 points between the 2 evaluations indicates a clinically significant change [42]. The internal consistency of the COPM is within a reasonable range, and test-retest reliability is well above acceptable levels. Furthermore, the validity of the COPM as a measure of occupational performance has been supported by a large number of studies [51].

The SES assesses self-efficacy (ie, individuals’ confidence in their ability). The social cognitive theory formulated by Bandura [44] is the base for self-efficacy and reflects an individual’s belief in their capability to perform activities to attain a desired result. The theory of self-efficacy proposes that the stronger a person’s efficacy expectations are, the more likely the person will start and continue performing these given activities. The persons with stroke will be instructed during the interview to rate how confident they are about performing each of 16 everyday activities on a 10-point rating scale ranging from 1=*not confident at all in my ability* to 10=*very confident in my ability*. The rating process takes approximately 10 minutes, and the responses are summarized into a total score. The SES (Multimedia Appendix 4) has been adapted from a similar scale for people with pain [52] and has been used in our previous feasibility study [33].

#### Family Members

The CBS will be used to describe the perceptions and characteristics of caregiver burden among the family members assisting the person with stroke [48].

The CBS assesses 22 items, reflecting factors that include the family members’ health, general strain, isolation, disappointment, emotional involvement, and environmental aspects. The measure is administered as a self-report questionnaire and takes 20 to 30 minutes to complete. Each item is rated on a 4-point scale (1=*not at all*, 2=*seldom*, 3=*sometimes*, and 4=*often*), with a higher score indicating a greater burden. The ratings on the items are summarized into a total score. No cutoff score is used. The measure has good construct validity and test-retest reliability [48].

### Secondary Outcomes

#### Persons With Stroke

The SIS 3.0 (Ugandan version) [46] will assess the self-perceived impact of stroke in 8 domains: strength, memory and thinking, emotions, communication, ADLs and instrumental ADLs, mobility, hand function, and participation. The SIS 3.0 (Ugandan version) includes 59 items within these 8 domains, and it is administered as a structured interview that takes approximately 30 minutes to complete. Aggregated scores for each domain are generated ranging from 0 to 100; the higher the score, the lower the perceived impact of stroke (ie, fewer problems in everyday life).

Most domains of the SIS 3.0 (Ugandan version) satisfy important criteria for rating scale functioning. The internal consistency and discriminant validity are satisfactory for use among people with stroke in Uganda [46].

The Scandinavian Stroke Scale will be used to describe clinical characteristics, assess neurological impairment, and define stroke severity. This scale is administered face-to-face and takes approximately 10 minutes to complete. It provides a score for stroke severity between 2 and 5 grades of deficit ranked in decreasing order based on the level of consciousness, eye movement, orientation, speech, hand and leg movement, gait, and facial paralysis; the lower the score, the worse the deficit. The interobserver reliability for the different components is very good, as is the agreement between the domains [53].

The BI will be used to assess independence or dependence in ADLs across 10 self-care and mobility activities [47]. The values assigned to each item (0, 5, 10, or 15) are based on the time and amount of physical assistance required if the person cannot perform the activity independently. Scores range from 0 to 100, with a lower score indicating greater dependency. The BI is administered through an interview that takes approximately 10 minutes to complete and is reliable and valid for people with stroke [54].

#### Family Members

The LiSat-11 will be used to measure global life satisfaction as well as satisfaction across 10 domains using a 6-point scale [49]. The LiSat-11 is completed through self-report, which takes approximately 10 minutes. The score on each domain is dichotomized and presented without summarizing the overall scores. The questionnaire has demonstrated acceptable test-retest reliability, specificity, and sensitivity [49].

Health care use will be collected through a structured interview with the person with stroke, together with the family member.

### Experiences of Taking Part in F@ce 2.0 Among Persons With Stroke and Their Family Members

Semistructured qualitative interviews (Multimedia Appendix 2) will be conducted face-to-face with persons with stroke and their family members. Interviews with the person with stroke (n=6-10) and family members (n=6-10) from both rural and urban areas will be conducted in their home setting after they complete the F@ce 2.0 intervention. Their experiences of participating in F@ce 2.0 will be explored, and the data from the interviews will be analyzed using a grounded theory approach [55]. The participant group will be selected to represent a range of experiences (eg, varied characteristics regarding sex, level of disability, and living conditions) to ensure the collection of rich qualitative data. An interview guide with open-ended questions focusing on participants’ everyday life experiences when participating in the F@ce 2.0 intervention will be used. Field notes will be taken during the interviews, and all interviews will be digitally recorded and transcribed verbatim and translated into English if conducted in Luganda. The transcripts from these interviews will also be used in the process evaluation described in the next subsection.

### Process Evaluation of F@ce 2.0 in the Ugandan Context

A process evaluation is essential for designing and evaluating complex interventions, such as F@ce 2.0, and refers to activities related to the implementation, acceptance, and reach of an intervention. A process evaluation aims to answer questions about how the intervention interacts with its context, how different perspectives from stakeholders can be integrated, or how the intervention can be refined [56]. This study will use a single-case study design with mixed methods, combining qualitative and quantitative data to explore the implementation process and mechanisms of impact of the F@ce 2.0 program. Quantitative process data will include metrics such as the mean number of minutes per session with clients, the number of telephone contacts between HCPs and clients, and data from the web platform. The HCPs’ logbooks will also be collected. In addition, semistructured interviews (Multimedia Appendix 2) will be conducted with persons with stroke, their family members, and the HCPs providing the intervention. The interviews with the persons with stroke and family members will focus on exploring their perceptions of the value, benefits, and detrimental or unintended consequences of the intervention, as well as their perspectives of the intervention’s acceptability, fidelity, reach, and dose. The interviews with HCPs will cover their reflections and reasoning in relation to preparations for delivering the intervention at the workshops, as well as the intervention delivery process, aiming to explore the implementation of the intervention. The logbooks maintained by the HCPs will include their field notes and reflections after the workshop and coaching sessions. These field notes will describe conditions that facilitated or hindered session delivery, as well as potential positive or negative side effects. The HCPs’ acceptability of the intervention will also be documented. From the web platform, information on response rates to SMS text messages as well as target achievement will be derived.

### Data Analyses

Anonymized data will be entered into SPSS for Windows (IBM Corp) [57]. The number of participants (persons with stroke and family members) being recruited will be presented in a flowchart according to the CONSORT statement [36,37]. The retention rate and adherence to the intervention (eg, responses to SMS text messages, HCPs’ follow-up meetings with the participants, and all other services related to the intervention, as well as the number of participants seen by each HCP or team) will be presented based on frequencies and percentages. Descriptive statistics will be used to present the characteristics of the participants, health care use, and the outcomes after the intervention and at 6 months.

All statistical analyses comparing the primary and secondary outcomes between the IG and the CG will be performed using intention-to-treat analysis [58]. For missing values, the imputation method of last value carried forward will be used. To assess differences in changes in primary outcomes between the IG and CG at the different data collection points, multivariate statistical methods will be used. Covariates will include sex, age, stroke severity, and independence and dependence in ADLs before stroke, as measured by the BI. The statistician will be blinded to the group allocation for the intervention.

The interviews with persons with stroke and their family members will explore their experiences of participating in F@ce 2.0, and we will analyze the interview data using a grounded theory approach [55]. The interviews will be transcribed verbatim. The interview material will be analyzed through constant comparison of the content in the transcripts. The material will be read several times to get to know the data profoundly. Next, the initial coding will be performed by coding the material line by line, followed by focused coding where the initial codes from each interview will be compared. In the next step, the codes will be compiled into categories and subcategories. The findings will present a meaning structure comprising a core category and subcategories of the studied phenomenon, that is, the meaning of participating in a mobile phone–supported and family-centered intervention and the implications for everyday life after stroke [55]. The qualitative data used in the process evaluation will be analyzed using content analysis [59]. In this analysis, meaning-bearing units will be identified, condensed, and abstracted to codes from each interview. The codes will be compared for similarities and differences and organized into categories and subcategories that will describe an abstract level of the content of all interviews [59].

All personal information (eg, names) will be removed during transcription. Copies of the digital recordings will be destroyed once transcription is complete. Interview transcriptions and all other data will be coded and stored in a secure electronic database.

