### Sample Size and Power Considerations

A power calculation based on the results from our pilot study in Uganda [33] regarding the primary outcome—a clinically important difference of 2 points according to the COPM (ie, perceived performance and satisfaction in daily activities)—showed that 36 participants in each group are needed. Considering an attrition rate of 25%, a total of 90 participants will be required (α set at .05 and β at .80).

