## Results

As of March 2024, a total of 100 participants with stroke had been enrolled in the randomized controlled trial, of whom 2 (2%) died of natural causes. A total of 96 family members had also been enrolled. The intervention has been performed via daily reminders sent by SMS text messages and phone calls twice a week by the interventionist. Data collection was initiated on January 25, 2022. All baseline and follow-up assessments have been completed. Data analysis is planned to start in October 2024 for the randomized controlled trial and it is planned to be submitted during May 2025. Data collection for the qualitative study and the process evaluation have been completed. Data analysis for the qualitative study will be initiated in February 2025. The process evaluation has been submitted to a scientific journal.

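### Last value carried forward is fixed as the missing-data rule: at the planned attrition it shrinks a true effect, and if loss differs between arms it can bias the comparison in either direction

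*Protocol article*

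**What the plan says.** Under Data Analyses, the article states that all analyses "comparing the primary and secondary outcomes between the IG and the CG will be performed using intention-to-treat analysis". The next sentence gives the missing-data rule: "For missing values, the imputation method of last value carried forward will be used". The comparison itself is then described: "To assess differences in changes in primary outcomes between the IG and CG at the different data collection points, multivariate statistical methods will be used". The rule has no exception, for death or anything else.

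Table 1 and the Data Collection section place the COPM, the Self-Efficacy Scale and the Caregiver Burden Scale at baseline, about week 9 and 6 months. The sample size section rests on "a clinically important difference of 2 points according to the COPM", reports that the calculation "showed that 36 participants in each group are needed", and adds: "Considering an attrition rate of 25%, a total of 90 participants will be required".

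The Results section reports 100 enrolled participants with stroke, "of whom 2 (2%) died of natural causes", without arm or timing. It says that assessments are finished but gives no count of missing values by arm.

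**The concern.** The comparison is of change between arms. With two follow-up visits, the rule can do only two things: enter a change of exactly zero for someone lost before week 9, or enter the week 9 score at 6 months for someone lost later. Both are hard to defend where improvement is expected. Control participants also receive rehabilitation from their centre, so gains are plausible in both arms. The filled-in scores are then analysed as if they had been observed.

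At stake are the estimate and p-value of every primary comparison. If the intervention works, its effect is diluted. If the arms lose different proportions, the rule removes more gain from one arm than from the other and creates a difference that is not due to treatment. Read literally, it would also give performance and self-efficacy scores to anyone who died before a scheduled visit.

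**Working it through.** **Inputs from the article.** COPM difference 2; 36 per group; 25% attrition; 90 in total; α 0.05 (taken as two-sided); power 0.80 (printed as β).

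**Assumptions not in the article.** SD 3.0; baseline–follow-up correlation 0.5 (so the SD of change is also 3.0); 45 per arm; control-arm gain of 2 to 3 points; loss random within arm; where week 9 is carried, 60% of the gain reached by then.

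**The plan's own figures.** n per group = 2(1.960 + 0.842)² × 3² / 2² = 35.3, rounded up to 36. The SD is therefore back-calculated: 36 is consistent with SD 3.0 but cannot be checked independently. For attrition, 72 × 1.25 = 90 reproduces the total (72 / 0.75 would give 96; that is a separate matter).

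**Expected difference when baseline is carried.** Let dI and dC be the proportions lost in the intervention and control arms, g the control gain and D the true effect:

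E = (1 − dI)(g + D) − (1 − dC)g

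- Equal 25% loss, D = 2: 0.75(g + 2) − 0.75g = 1.5, a 25% attenuation for any g.
- If half the dropouts carry week 9 instead, the share of gain retained is 0.75 + 0.125 × 0.6 = 0.825, and 0.825 × 2 = 1.65.
- 35% v 15% lost (intervention v control), D = 2, g = 3: 0.65 × 5 − 0.85 × 3 = 0.70, a bias of −1.3.
- 15% v 35% lost, D = 2, g = 3: 0.85 × 5 − 0.65 × 3 = 2.30, a bias of +0.3.
- Equal 2% loss, D = 2: 0.98 × 2 = 1.96, a bias of −0.04.

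**Type I error by hand (D = 0, change scores, 15% v 35% lost, baseline carried).** The variance of change in an arm with loss d is (1 − d) × 9 + d(1 − d)g².

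- g = 2: variances 8.16 and 6.76; SE = √(14.92/45) = 0.576; spurious difference (0.85 − 0.65) × 2 = 0.40; shift 0.40/0.576 = 0.695; rejection P(Z > 1.265) + P(Z < −2.655) = 0.107.
- g = 3: variances 8.80 and 7.90; SE = 0.609; spurious difference 0.60; shift 0.985; rejection about 0.166.

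**Simulation (ANCOVA on baseline, D = 0, 4,000 runs per scenario).** Ranges cover g = 2 and 3, with all dropouts carrying baseline or half carrying week 9.

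| Missing, intervention v control | Spurious difference | Rejection rate |
|---|---|---|
| 25% v 25% | about 0 | 0.045–0.054 |
| 20% v 30% | 0.13 to 0.30 | 0.056–0.082 |
| 15% v 35% | 0.27 to 0.61 | 0.078–0.194 |
| 35% v 15% | −0.29 to −0.60 | 0.084–0.192 |

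A separate run for 15% v 35%, with g = 2 and half the dropouts carrying week 9, gave 0.28 points and 7.4%. ANCOVA on observed 6-month values stayed between 0.046 and 0.058 throughout, as it should when loss is simulated as random within arm.

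**Power at equal 25% loss, D = 2.** With ANCOVA and baseline carried, 0.65–0.74 against about 0.87 on observed data; with half carrying week 9, 0.78–0.81. In a change-score analysis with control gains of 0 to 1 point, 0.73–0.76 against 0.77. The loss of power depends heavily on the analysis and on the gains assumed.

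**The case against.** The strongest reply is that everything depends on missingness that nobody outside the trial has seen. The 25% is a planning allowance, not a result. At 5% v 10% lost with a 2-point gain in both arms, the spurious difference is (0.95 − 0.90) × 2 = 0.10 points and the rejection rate 5.1%. Near 2% missing there is little to argue about. The 15% v 35% split is an assumption, and carrying baseline for every dropout is the harsher timing case. All of this stands and limits the size that can be claimed.

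Four stronger readings are tempting, and the article does not support them:

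- **That the rule always biases the result or always inflates type I error.** With equal random loss and no true effect, the difference is unbiased and the test keeps its level.
- **That loss is higher among controls, so the rule favours F@ce 2.0.** Controls do have less contact. However, both arms share the assessment schedule, the data collectors are not involved in delivery, and the payment at each data collection point is the same. Frequent messages and calls might also burden the intervention arm. No direction can be inferred.
- **That the 2 deceased participants will be given scores.** If they died after the 6-month visit, nothing would be imputed.
- **That no sensitivity analysis exists.** An analysis plan not shown may contain one. What can be criticised is the rule that the article itself fixes.

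The opposite defence, that carrying values forward is at least conservative, also fails: with a true effect of 2 points the bias ran from −1.3 to +0.3, and with no effect the error rate can rise.

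A likelihood-based model is not free of assumptions either. It needs missing at random, and if baseline is only a covariate it drops participants with no follow-up value.

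**Conclusion.** The point holds in conditional form and should be fixed. The article fixes a missing-data rule that does not perform acceptably at the attrition the trial planned for. With SD about 3 and loss random within arm, equal 25% loss reduces a true 2-point COPM difference to about 1.5–1.65. Unequal loss with improvement in both arms can bias the estimate either way and raise type I error to roughly 6–8% (20% v 30%) or 7–19% (15% v 35%), depending on the gain and the timing of loss. If realised missingness is near 2% and balanced, the practical effect is negligible. Imputation after death follows from the literal wording only for deaths before a scheduled visit.

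**What to change.** Replace the sentence in Data Analyses, and document and date the change before unblinding:

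- **Primary analysis:** a mixed model for repeated measures on all observed values, with arm by visit, baseline score by visit and the covariates already listed, stated to be valid under missing at random.
- **Participants without follow-up data:** keep them either by including baseline as a response in a constrained longitudinal model or by multiple imputation.
- **Deaths:** do not impute values after death. Report deaths by arm and timing, and state how visits after death are treated, because a mixed model otherwise handles them as ordinary missing data.
- **Sensitivity:** add an analysis for departures from missing at random, for example delta-adjusted multiple imputation. Keep last value carried forward only as a sensitivity analysis.
- **Reporting:** give missingness by arm and visit, so that readers can judge how much the choice matters.

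The cost is a documented change of method after data collection and a little more analysis work. No new data are needed, and mixed models can be fitted in SPSS, the software named. The article plans the trial analysis from October 2024 with a statistician blinded to allocation, which makes a change before unblinding credible. If unblinding has already taken place, the change should be reported as made afterwards, with both analyses shown.
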